Until now and to the best of our knowledge, no study using a comparable computer based body exposure intervention using photographs of the own body could be identified. Because of this, sample size calculation for the current pilot study was performed in accordance with former studies assessing effects of mirror (body) exposure in adolescents and adults with EDs (23, 42), as well as fear-stimulus exposure in phobic adolescents (48), reporting mostly medium effect sizes for body avoidance (body) anxiety and negative emotions. According to sample size calculations [G^*^Power; (49)] based on default values (alpha error =.05, power =.80) and the assumption that effect sizes for the RCT (AN-INT vs. AN-TAU) are expected to be larger than for the comparison of AN-INT vs. CG-INT, both taking part in the same intervention, at least 23 participants are required for the intervention groups (AN-INT, CG-INT) and at least 15 participants are required for AN-TAU. This is calculated based on a 2 × 2-mixed design (RCT; between-subject factor: AN-INT vs. AN-TAU; repeated measure within-subject factor: pre, post) and a 2 × 4-mixed design (AN-INT vs. CG-INT; repeated measure within-subject factor: 4 exposure sessions), respectively.

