### Data Analysis

Research questions will be analyzed in repeated measures (rm)-AN(C)OVAs, considering within-subject and between-subject factors and interpreting—depending on the respective hypothesis—main and/or interaction effects. To test intervention effects on body dissatisfaction, body control and body avoidance, as well as AB comparing AN-INT vs. AN-TAU within the RCT, a 2 × 2-rm-AN(C)OVA (between-subject factor = group: AN-INT vs. AN-TAU; within-subject factor = time: pre, post) will be conducted. To assess modifications within and throughout the body exposure sessions regarding AB, emotion ratings, HR, HRV, as well as cortisol and sAA reactivity slope, a 2 × 4-rm-AN(C)OVA (between-subject factor = group: AN-INT vs. CG-INT; within-subject factor = time: 4 exposure sessions) will be conducted. Potential confounders are derived from a theoretical point of view (e.g., age, depression) and will be included as covariates in the statistical analyses (ANCOVAs). Specific test requirements will be tested prior to performing the full analysis. In case of non-adherence to the test requirements (i.e., normal distribution and variance homogeneity), the outcome measures will be logarithmized and additional non-parametric tests will be calculated. Data will be analyzed using IBM SPSS Statistics software. Significance level will be set at *p* =.05 and effect sizes will be interpreted. Effect sizes for AN(C)OVA results were computed as partial η^2^ ($\eta_{\text{p}}^{2}$), with values $\eta_{\text{p}}^{2}$ <0.06 interpreted as small,.06 ≤ $\eta_{\text{p}}^{2}$ <0.14 as medium and $\eta_{\text{p}}^{2}$ ≥ 0.14 as large effects (64). Correction for multiple testing will be applied if necessary.

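### Logs and rank tests do not in general correct unequal variances in a 23 vs 15 comparison; a Welch or HC3 analysis should be named in advance for the questionnaire outcomes

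*Protocol article*

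**What the plan says.** The Data Analysis section plans the randomised comparison as "a 2 × 2-rm-AN(C)OVA (between-subject factor = group: AN-INT vs. AN-TAU; within-subject factor = time: pre, post) will be conducted", at a significance level of .05. It covers body dissatisfaction (the primary question in Objectives), body checking and avoidance, and attentional bias.

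On assumptions the section says "Specific test requirements will be tested prior to performing the full analysis". It then gives one response to failure of either requirement: "In case of non-adherence to the test requirements (i.e., normal distribution and variance homogeneity), the outcome measures will be logarithmized", with non-parametric tests added. No method that allows unequal variances is named.

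The Target/Study Population section gives the sizes: "at least 23 participants are required for the intervention groups (AN-INT, CG-INT) and at least 15 participants are required for AN-TAU". These are minimums. No SD, variance ratio, effect size or pre-post correlation is stated.

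**The concern.** This is a stated rule with a trigger and a remedy, so it is not a detail left for a later document. For variance heterogeneity the remedy does not match the trigger. An F test on logged scores still pools the two arms' variances. A rank test also drifts from its nominal level when spreads differ and arms are unequal. With equal arms this would hardly matter; the planned 23 vs 15 makes it matter.

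The primary randomised test is at stake. If change scores vary more in AN-INT, which variable response to exposure would produce, the test is conservative and loses power in an already small study. If they vary more in AN-TAU, it rejects too often. In neither case does the planned sequence bring the test back to its stated level.

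**Working it through.** **Inputs from the article.** Level .05; arms of 23 and 15; two time points; pooled-variance rm-ANOVA. The figures 23 and 15 cannot be reproduced, because the effect size is described only as mostly medium and no correlation is given. Only the counts are used below.

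**Assumptions (not in the article).** Normal scores, equal mean change, and a ratio of the SDs of change (AN-INT:AN-TAU) between 1:2 and 2:1. For the log and power runs: pre-score mean 35 and SD 7, SD of change 5, 7.5 or 10.

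**Step 1: reduce the test.** With two time points, the group x time F is the square of the pooled two-sample t on the change score, with 23 + 15 - 2 = 36 degrees of freedom and critical value 2.028.

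**Step 2: compare the pooled variance of the mean difference with the true one.**

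- Pooled: [(22·s₁² + 14·s₂²)/36]·(1/23 + 1/15), where 1/23 + 1/15 = 0.1101
- True: s₁²/23 + s₂²/15

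AN-INT more variable, 2:1: pooled = (102/36)·0.1101 = 0.312; true = 4/23 + 1/15 = 0.241. The standard error is overstated by √(0.312/0.241) = 1.14. The effective critical value is 2.028·1.14 = 2.31, a level of about 2.7%.

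AN-TAU more variable, 1:2: pooled = (78/36)·0.1101 = 0.239; true = 1/23 + 4/15 = 0.310. The factor is √(0.239/0.310) = 0.877. The critical value is 1.78, a level of about 8.4%.

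The same steps at 1.5:1 and 1:1.5 give factors 1.087 and 0.920, and levels of about 3.4% and 7.0%.

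**Step 3: simulation.** Type I error in %, 23 vs 15; 40,000 trials per setting for the rows with unequal SDs:

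| SD ratio AN-INT:AN-TAU | Pooled F | F on logs | Rank test | Welch |
|---|---|---|---|---|
| 1:1 | 5.1 | about 5 | 4.9 | 5.0 |
| 1.5:1 | 3.4 | 3.2 | 4.1 | 4.9 |
| 2:1 | 2.7 | 2.6 | 3.9 | 4.9 |
| 1:1.5 | 7.1 | 7.3 | 6.1 | 5.1 |
| 1:2 | 8.6 | 9.5 | 7.2 | 5.0 |

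Independent runs agree to within a few tenths of a point. From 1:3 to 3:1, Welch stays at 4.9% to 5.2%. ANCOVA with HC3 errors runs at 4.1% to 5.0%; with HC2 errors it reaches 6.1%. With 19 per arm, the pooled test is 5.4% even at an SD ratio of 2.

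**Step 4: the pre-test.** Levene's test on change detects a 1.5:1 ratio 31% to 35% of the time at these sizes, or 26% to 27% when median-centred.

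**Step 5: power with AN-INT more variable.** At 1.5:1 and a mean difference of about 6.5, Welch gives about 88% against 84% for the pooled test. At 2:1 and a difference of about 8, it gives about 88% against 82% to 83%. That is roughly 4 to 6 points. Where the pooled test starts from 77%, the gains are about 5 points (1.5:1) and 7 to 8 points (2:1). With equal SDs, Welch has 82.8% against 83.3%.

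**The case against.** A reader might infer that the trial's randomised test runs at 3% to 9% instead of 5%. The documents do not support that. They give no SD ratio, and the range needs one of 2:1, a fourfold variance ratio. If the intervention affected nobody, randomisation would give both arms the same distribution and the level would be 5%. The distortion needs equal mean change with unequal spread.

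The 2:1 case is also demanding. With SDs of change of 10 and 5, independent individual effects of the intervention would need an SD of √(100 - 25) = 8.7 around a mean of zero. Even 1.5:1 needs √(56.25 - 25) = 5.6. Variable response to exposure would make AN-INT more variable, so it supports only the conservative, power-losing side. No mechanism is at hand for the 7% to 9% side.

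The fallback is not useless either. The plan adds rank tests to the logs, and the rank test moves the level part of the way back. The simulated scores are symmetric with equal means, a setting in which logs cannot stabilise variance. Where spread grows with the mean, as fixation times may behave, logging is a standard variance remedy. It would therefore be wrong to infer that logs should be dropped for every AN-INT vs AN-TAU outcome. Finally, 23 and 15 are minimums, so the realised imbalance may be smaller, and this is a pilot whose effect sizes will be interpreted alongside its p values.

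All of this stands and limits the size and reach of the point. It does not remove it: the rule names unequal variances as a trigger and answers with methods that do not in general correct them at the planned sizes.

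**Conclusion.** The concern holds in conditional form. If the SDs of change differ 1.5:1 to 2:1 with equal mean change and arms of 23 and 15, the pooled or log-scale F runs at about 3.3% to 2.7% when AN-INT varies more and about 7% to 9% when AN-TAU varies more. The rank test runs at about 4% and 6% to 7% respectively, and Welch at about 5%. With equal SDs nothing is wrong. The likelier cost is lost power, roughly 4 to 6 points in the scenarios with pooled power a little above 80%.

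These figures rest on an assumed SD ratio, normal symmetric scores and the minimum arm sizes. They concern the questionnaire outcomes of the randomised comparison. They do not show that the trial's actual error rate is wrong, or that logging is unsuitable for skewed measures.

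**What to change.** Add one sentence to the Data Analysis section. For the questionnaire outcomes in AN-INT vs AN-TAU, including body dissatisfaction as the primary one, the governing analysis is a Welch test on pre-post change, or the linear model with HC3 standard errors when covariates are included, whatever the variance pre-test shows. Keep log transformation for outcomes that are skewed or whose spread grows with the mean, such as fixation times, and keep rank tests as sensitivity analyses.

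The cost is slightly fewer effective degrees of freedom. About 0.5 point of power is lost if the variances are in fact equal, and HC3 is slightly conservative (down to about 4.1% in the settings checked).

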## Objectives

Due to the high association of BI disturbances and the development and maintenance of EDs, including AN, psychotherapy with patients with AN in any setting should include modules treating body image disturbances explicitly (8). A need for new, emerging treatments with a focus on brain-based interventions as well as mechanism-based approaches, which are specifically addressing psychopathology and BI disturbances, have been proclaimed (43, 44). While there is data available on the efficacy of body exposure interventions for reducing BI disturbances in women with EDs and high body dissatisfaction (20, 25), there is a lack of available data regarding the efficacy of body exposures with children and adolescents. Furthermore, different EDs are frequently mixed up in the literature, making it difficult to investigate specific processes, which might differentiate between body dissatisfied individuals with EDs and body dissatisfied individuals without EDs. Also, underlying psychophysiological and neurobiological processes during body exposure are still poorly understood. Therefore, the aim of this study is to investigate the short-term efficacy of a computer-based body exposure intervention for adolescents with AN. This group is being compared to an AN-TAU group and a body dissatisfied clinical control group.

The primary research question is: Is body dissatisfaction in adolescents with AN reduced after completing a four-session computer based body exposure intervention, compared to TAU?

Secondary research questions include: (1) Body checking and avoidance: Can four sessions of a computer based body exposure intervention reduce body checking and body avoidance behavior, compared to TAU? (2) Viewing patterns / attentional bias (AB): Can the AB in terms of focusing more on negatively rated body parts, measured via eye tracking, be reduced by a four-session computer based intervention in adolescents with AN, compared to TAU? Are there AN-specific AB modifications in comparison to a body dissatisfied control group also obtaining the intervention? (3) Stress reactivity: Do four sessions of body exposure modify stress reactivity in terms of a physiological habituation, measured via salivary cortisol, sAA, HR and HRV? Are there AN-specific effects in physiological habituation in comparison to a body dissatisfied clinical control group?

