### Parameters

Psychopathology is assessed through the completion of multiple questionnaires: Eating disorder psychopathology and body dissatisfaction are assessed by administering the Eating Disorder Inventory-2 [EDI-2 (50), German version (51)], body image avoidance behavior via the Body Image Avoidance Questionnaire [BIAQ (52), German version (53)], and body checking behavior by the Body Checking Questionnaire [BCQ (54), German version (55)]. To assess relevant comorbid symptoms, we are also administering the Beck Depression Inventory-Revised [BDI-II (56), German version (57)] to test for depressive symptoms, and the Fear Survey Schedule for Children-Revised [FSSC-R (58), German version (59)] to test for symptoms of anxiety. Additionally, body parts are rated for self-perceived attractiveness on a seven point Likert-type scale (ranging from very negative to very positive) and participants are asked to list their three most disliked body parts. In order to control for a potential attention deficit we also administer an attention test [d2 test (60).

Attentional bias is assessed by recording gaze patterns during body exposure via the Eyegaze Analysis System^TM^ (Interactive Minds, Dresden, Germany), which is an infrared video-based binocular tracking system (17). In particular, the subsequent analysis is focused on assessing the fixation patterns (duration, frequency) on the previously three most negatively rated body parts, which are defined as regions of interest (ROI). A fixation is counted if the participant's gaze is focused on a specific area for 100 ms or more. Total fixation time for each ROI is calculated and corrected for its size relative to the picture size (17).

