Stress levels and stress reactivity are assessed through multiple measures. Firstly, subjective emotion ratings (anxiety, anger, disgust, stress, and sadness) are obtained on a ten-point Likert scale before, during, directly after, and 30 min after each exposure session. Secondly, participants' cardiac activity is monitored during the exposure sessions using a Scosche^®^ Rhythm 24 Heart Rate monitor. Raw data is further processed using Python (https://www.python.org/). RR intervals (RRI) will be detected by a peak-detection algorithm and outliers will be removed using implemented python libraries (e.g., hrv-analysis 1.0.4 package). Instantaneous heart rate (IHR), as a measurement of heart rate variability (HRV), will be derived following IHR$=\frac{60000}{RRI}$, where RRI are measured in milliseconds (61). Changes in HR/IHR and RRI in relation to the number of exposure sessions, i.e., changes over the course of the four exposure sessions, will be analyzed. Thirdly, saliva samples are taken before, during (10 min into the exposure), directly after and 30 min after the body exposure using Salivettes^®^ (Sarstedt, Nümbrecht, Germany). Cortisol, as well as sAA, levels are subsequently analyzed in the laboratory. To do this, saliva samples are stored at −20°C until processing. When processing begins, the samples are thawed and centrifuged at 2,000 × g and 20°C for 10 min. To analyze salivary free cortisol, a commercial chemiluminescence immunoassay (CLIA; IBL Hamburg, Germany) is used, following the manufacturer's instructions. Similarly, to measure sAA, a quantitative enzyme kinetic method is employed, following a standardized protocol.

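### One data-dependent log-and-rank fallback covers every outcome: it cannot be computed for some of them, can worsen left-skewed scores, and leaves the scale of the primary effect open until the data are seen

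*Protocol article*

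**What the plan says.** All statements are in the protocol article.

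- **Primary question (Objectives).** "Is body dissatisfaction in adolescents with AN reduced after completing a four-session computer based body exposure intervention, compared to TAU"? The instrument is named under Parameters: "Eating disorder psychopathology and body dissatisfaction are assessed by administering the Eating Disorder Inventory-2". Its score range and expected distribution are not given.
- **Planned tests (Data Analysis).** A 2 × 2 repeated-measures AN(C)OVA (AN-INT vs AN-TAU, pre and post) covers body dissatisfaction, checking, avoidance and attentional bias. A 2 × 4 version (AN-INT vs CG-INT, four sessions) covers attentional bias, emotion ratings, heart rate measures and the cortisol and alpha-amylase reactivity slope.
- **Fallback (Data Analysis).** "Specific test requirements will be tested prior to performing the full analysis". The trigger is worded "In case of non-adherence to the test requirements (i.e., normal distribution and variance homogeneity", and the consequence is that "the outcome measures will be logarithmized and additional non-parametric tests will be calculated".
- **Attentional bias (Parameters).** Only fixations of at least 100 ms count. "Total fixation time for each ROI is calculated and corrected for its size relative to the picture size".
- **Ratings with a stated range (Parameters).** Attractiveness is rated on a "seven point Likert-type scale (ranging from very negative to very positive"). Emotion ratings "are obtained on a ten-point Likert scale before, during, directly after, and 30 min after each exposure session".

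**The concern.** A log transformation suits positive, right-skewed quantities. The sentence prescribes it for everything that fails a check, including outcomes that can be zero, outcomes that can be negative, and bounded scores that may be skewed the other way.

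The choice of scale is also made on the trial data, after a check in groups of about 23 and 15. If the check passes, the primary effect is a difference in points; if it fails, it is in effect a ratio. In the second case a logged result and a non-parametric result stand side by side, and neither is said to decide. A simple rank test on change also does not reproduce a group-by-time interaction with covariates, which the same section foresees.

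At stake are an attentional-bias or slope analysis that loses or breaks on some values, and a primary result whose scale is unknown in advance. The second matters for a pilot whose stated use is to orient the effect sizes of a larger trial.

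**Working it through.** **1. Where the rule cannot be computed.** This needs no assumption about distributions.
- *Fixation time.* Each free-viewing window lasts 30 s per view. A region with no fixation of 100 ms or more scores 0. Correction for region size multiplies or divides by a constant, so 0 stays 0, and log(0) is undefined. The documents do not say how often this would happen. If fixations per region were Poisson with mean k, P(0) = exp(-k): 37% for k = 1, 14% for k = 2, 5% for k = 3 and 0.7% for k = 5. The expected benefit is less time on disliked body parts, so a working intervention moves values towards zero, and lost zeros would not be random.
- *Reactivity slope.* A slope can be zero or negative, and the article expects neuroendocrine levels to fall within and across sessions. The log of such a slope is undefined.

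**2. Effect on bounded scores.** Assumptions not in the documents: a 9-54 scale, and normal scores with SD 10 rounded and clipped to the range. Skewness, raw then logged:

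| Score | Raw | Logged |
|---|---|---|
| 9-54, mean 38 | -0.24 | -1.13 |
| 9-54, mean 42 | -0.45 | -1.22 |
| 9-54, mean 46 | -0.73 | -1.38 |
| 10-point rating, mean 7 (SD 2.5) | -0.38 | -1.68 |
| 7-point rating, mean 2.2 (SD 1.3) | +0.60 | -0.16 |

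The log worsens left skew and helps right skew. With means of 42 and 46, a Shapiro-Wilk check on the four group-by-time cells fired in 53% and 94% of trials. After logging, the data still failed in 98% and 99.9% of those trials. The article names neither the check nor what it is applied to, so these rates only illustrate.

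**3. Effect on the primary test.** In a 2 × 2 mixed design without covariates, the interaction is the two-sample t-test on change (F = t²), so change scores were compared. Inputs: 23 and 15 participants (the article's minimum numbers), alpha 0.05. Assumptions: a Beta(3, 1.2)-shaped score rescaled to 9-54, latent pre-post correlation 0.6, and 4,000 trials per scenario. One Monte Carlo standard error at 5% is √(0.05 × 0.95 / 4,000) = 0.34 points.
- Mean skewness goes from about -0.65 to -1.17, and the check fires in about 63-74% of trials.
- Type I error: raw change 4.7%, logged change 4.6%. Accepting log or rank gives 5.9%; accepting raw, log or rank gives 6.2%.
- Log and rank disagree on significance in about 3-9% of trials, depending on the true effect.
- Power at a latent shift of 0.8 SD: raw change 74.6%, logged change 72.9%, raw baseline-adjusted ANCOVA 79.3%, logged ANCOVA 75.6%.
 - Cost of logging the change score: 74.6 - 72.9 = 1.7 points. At 1.0 SD it is 92.2 - 91.6 = 0.6 points.
 - Gain from baseline adjustment on the raw scale: 79.3 - 74.6 = 4.7 points.
 - Cost of logging within ANCOVA: 79.3 - 75.6 = 3.7 points.

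**4. Same test under the clipped-normal scores (correlation 0.6).** Type I error for raw, log and rank was 5.8, 5.9 and 5.7% (mean 42) and 5.5, 5.6 and 5.2% (mean 46). Accepting any of the three gave 7.7% and 6.9%, which is 1.9 and 1.4 points above the raw test. With a true drop of 6 to 7 points, log and rank disagreed in about 10% of trials.

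The article's sample size cannot be reproduced exactly, because it states neither an effect size nor a pre-post correlation. Nothing here depends on it.

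**The case against.** **The scale may not matter much for the test.** A reader might infer that following the rule gives a worse primary analysis than leaving the scores alone. The figures do not support that: type I error is the same on both scales, and the planned change-score test loses only about 2 points of power. Setting raw ANCOVA (about 80%) against logged change (about 73%) mixes two changes, and most of that gap is baseline adjustment. This objection stands.

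**The left-skew point is conditional.** The article gives no EDI-2 range or distribution. A reader might point to the control group's selection above the 75th percentile, but that group is not in the randomised comparison, and AN participants have no body-dissatisfaction threshold for entry. Nor does a log worsen bounded scores in general, as the 7-point example shows. This stands too.

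**The rule does not offer a free choice.** Once triggered, it gives logged outcomes plus further non-parametric tests, and the word for the latter reads most naturally as supplementary. So about 5.9% is a closer figure than one that also counts the raw test, and even that requires accepting whichever result is significant, which the article does not say will be done.

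**An article condenses.** The deciding result, the named rank test and any offset may be in a fuller plan. That is fair for omissions. It does not cover a rule that the article states for all outcomes and that cannot be applied to some of them. One could read the log as applying to concentrations before slopes are formed, but the variable named for the analysis is the slope.

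**Conclusion.** The point holds in a limited form. The fallback is badly fixed as written:

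- It cannot be computed for zero fixation times or for zero or negative slopes. This follows from the article's own definitions; how often it would occur is unknown.
- It makes the scale of the primary effect depend on an unspecified check of normality and variance homogeneity in about 38 participants (23 + 15), and names no deciding result.
- It can increase left skew in bounded scores. This is plausible for body dissatisfaction in anorexia nervosa, but rests on an assumed range and shape.

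The numerical harm to the primary test is modest. Under the assumed Beta-shaped scores, log and rank disagree in about 3-9% of trials, type I error is about 5.9% if either is accepted (about 6.2% if raw is also allowed), and logging costs about 2 points of power. The clipped-normal scores give up to 7.7% if any of the three is accepted. The main reason to act is that the rule is inexecutable for named outcomes and the primary scale is unfixed, not a large error rate. The sentence should be changed before the data are analysed.

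**What to change.** Replace the sentence with a scale fixed in advance for each outcome:

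- **Questionnaire scores and ratings** (EDI-2, BIAQ, BCQ, attractiveness, emotions): untransformed. For AN-INT vs AN-TAU, the decisive analysis is ANCOVA of the post score adjusted for the pre score, with bootstrap or permutation inference if residuals are non-normal.
- **Cortisol and alpha-amylase:** log the concentrations in all cases, before slopes are computed; never log the slopes.
- **Fixation time:** untransformed with a permutation test, or log(x + c) with the constant c stated in advance.
- **Rank tests:** sensitivity analyses only.

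The cost is a few lines of analysis-plan wording and a bootstrap or permutation routine. The small downside is giving up the freedom to choose the scale after seeing the data. Baseline adjustment is a separate improvement; under the assumptions above it adds about 5 points of power (74.6% to 79.3%).
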